## Abstract

**Background::**

Chronic obstructive pulmonary disease (COPD) has a significant impact on quality of life and is costly to the health care system. It has been demonstrated that a self-management program improves quality of life, but programs are not universally available and telehealth interventions can provide home-based support, but have mixed results.^[1]^

**Aim::**

The aims of this study are to (1) assess the feasibility and acceptability of a 6 weeks’ educational program related to self-management with remote monitoring for Lebanese COPD patients; (2) pre-test its impact on quality of life, emergency visits, and rate of rehospitalization, and (3) to make recommendations for a future randomized trial.

**Methods::**

Validated questionnaires will be adapted to meet the context of our study in terms of acceptability, adoption, adequacy, fidelity, cost, and coverage. The impact of this program on quality of life will be measured with the COPD assessment test (CAT) and the COPD clinical questionnaire (CCQ), and the Hospital Anxiety and Depression (HAD) scale will be used to measure anxiety. All measures will be delivered pre- and post-intervention. To evaluate the impact of our program on the rate of hospitalization and emergency visits, the number of hospitalizations and emergency room visits during the year preceding the intervention will be collected from the hospital register of each participant.

**Discussion::**

This study is the first to evaluate the application of telehealth to optimize COPD management in Lebanon. The results of this study will provide evidence regarding the efficacy and feasibility of this approach for Lebanese patients with moderate to severe COPD.

## Introduction

1

Chronic obstructive pulmonary disease (COPD) is a progressive lung disease causing breathlessness, cough, fatigue, reduced exercise capacity, and frequent infections, with high societal burden.^[2]^ Medication optimizes airway function and reduces symptoms, but cannot address the psychosocial impact of the disease, including anxiety and depression,^[3]^ social isolation, and loss of independence and self-esteem.^[4]^

COPD is a major cause of morbidity and mortality worldwide. According to the Global Burden of Disease (GBD), COPD rose from the eighth to the fifth leading cause of GBD from 1990 to 2013.^[5]^ In 2013, COPD was the fourth leading cause of death globally, and it is predicted to become the third leading cause by 2020.^[6]^ It is the only major disease among the top 10 with a steadily increasing prevalence,^[7]^ and studies estimate that one in four persons will develop the disease in their lifetime.^[8]^ In 2010, a national study conducted in Lebanon revealed a proportion of 9.7% of COPD cases according to the GOLD definition, 80% of which were undiagnosed.^[9]^

Severe acute exacerbations COPD are associated with high rates of rehospitalization,^[10]^ worsened symptom severity,^[11]^ decreased exercise tolerance and physical activity,^[12–16]^ and negative impact on quality of life^[12]^ and mental health.^[13]^ In addition, care gaps in areas such as pharmacotherapy, inhalation technique, and knowledge of the disease are prevalent.^[17]^ Therefore, because of the burden of COPD to the health care system, the focus of its treatment has been shifting gradually from acute emergency care to a care that emphasizes self-management and maintenance.^[18]^

Self-management support interventions in COPD have been shown to improve health-related quality of life, exercise capacity, and self-efficacy^[19]^ and reduce COPD-related hospital admissions.^[20]^ As for telehealth approaches for COPD patients, several studies have reported improved knowledge and awareness of symptoms and health status.^[21,22]^ However, other studies have mixed results for self-efficacy.^[23]^ These controversies may be caused by the heterogeneity of the interventions.^[1]^

To date, in Lebanon, there are no structures for the education and care of patients with COPD. When a person with COPD is admitted to the hospital, doctors and nurses focus on their immediate problem and not on the chronicity of the disease, their overall health, or quality of life; they tend to talk to the patient about their illness rather than teach them how to manage it on a daily basis, to avoid the risk of exacerbation. Hence the need for a self-management program adapted to the Lebanese context.

The Neith program aims to study the impact of a nursing consultation and remote monitoring on the skills, knowledge, and quality of life of Lebanese patients with COPD and consists of four studies. The first study was a scoping review and showed that 4 components are essential in a self-management program for patients with COPD: initiation to the self-management program, educational sessions, support methods, and monitoring methods. The second one was a phenomenological qualitative study of 50 semi-directive interviews with Lebanese COPD patients was conducted to explore the experience of COPD patients with their disease in Lebanon, and showed that family support was a key factor in managing the disease. This third study will suggest recommendations that will lead to a fourth randomized study.

Thus, the aims of the present study are to

(1)explore the feasibility and acceptability of a remote monitoring and a self-management program for Lebanese patients with COPD,(2)pretest the impact of this program on the quality of life, emergency visits and rehospitalization rates for this population, and(3)make recommendations for a future randomized study.

This study will also potentially offer a framework in which COPD care can be managed in Lebanon. The present manuscript describes the protocol of the study.

## Methods

2

### Design

2.1

This study aims to evaluate the feasibility, acceptability and pre-test the impact of a nursing consultation and tele-monitoring in Lebanon. It will be conducted at the Hôtel-Dieu de France (HDF) hospital, one of the largest university hospitals in Beirut, and will use quantitative and qualitative methods in pre- and post-intervention to collect data over a period of 3 months with a single group intervention. Data will be collected by 2 researchers. A consent form will be signed by each participant before the intervention. Patients will be informed about the purpose of the study, the course of the intervention, and the freedom to withdraw from the study at any time. Their consent for the video recording will also be taken.

### Ethical aspects

2.2

This study has been approved by HDF Ethics Committee record CEHDF 1519, November 4, 2019. It will be conducted in accordance with the protocol. The rules of confidentiality will be respected.

### Setting and participants

2.3

An accidental empirical sample will be recruited based on the judgment of the pulmonologists at HDF hospital and on a voluntary basis from 30 patients with moderate to severe COPD.

To be considered eligible, in addition to signing the informed consent, patient must be adult (18 years of age or older), male or female, outpatient, with moderate (Gold 2) or severe (Gold 3) COPD, cognitively capable, with an adequate health status to participate in the study according to the clinical consensus between nurses and physicians.

Patients will be excluded if they are diagnosed with lung cancer or if they have cognitive problems related to memory loss or speech disorders that would not allow a constructive exchange.

### Intervention development

2.4

This intervention is based on the recommendations of the High Authority of Health (HAS) in France to plan a therapeutic education program (ETP),^[23]^ and on the D’Ivernois and Gagnayre model to build the educational diagnosis and plan the educational sessions.^[24]^ Health literacy will be assessed by the question proposed by Chew (Fig. 1).^[25]^ Our intervention will be based on the following framework and will consist of 3 phases (Fig. 2):

**Figure 1 F1:**
[figure not shown]
Framework of the intervention.

**Figure 2 F2:**
[figure not shown]
Progress of the intervention.

**Phase I:** At the end of a medical consultation, the doctor will offer the patient the opportunity to benefit from a nursing consultation and remote monitoring to better manage his COPD. A nursing consultation will be scheduled during which the nurse will explain the procedure, obtain the written consent of the patient, and develop an educational diagnosis with the participation of the patient. This step consists of a motivational interview that constitutes a guided, person-centered approach aiming at making patients aware of their behavior and consider actions to change it if it adversely affects their health. The nurse will explain how the patient should use the oximeter to measure daily the oxygen saturation (SaO2) and pulse, and how the information collected will be transmitted. An appointment will then be made for a first meeting at the patient's home.

**Phase II:** During the next 6 weeks the patient will receive one visit per week from the nurse to encourage him/her to self-assess each of his/her risk factors so that he/she becomes aware that his/her illness is not inevitable and that he/she can be involved in a behavioral change to reduce the risk of exacerbations. During these 6 weeks, a telephone number will be available to the patient in case of emergency and for any additional information.

**Phase III:** Following the 6 educational sessions delivered by the nurse, a final consultation will be scheduled at the nurse office to evaluate the patient's achievements and modify his/her educational assessment. A telephone follow-up will be conducted after one month to assess the maintenance of learning.

### Outcome measures

2.5

Based on Proctor's lists of outcome variables that can assess program implementation,^[26]^ this study will evaluate the acceptability, adoption, adequacy, fidelity, cost, and coverage of the intervention, using various tools: the “Pre-Referral intervention team inventory” will be adapted to study the acceptability of the intervention,^[27]^ the “adoption of information technology innovation” scale for adoption,^[28]^ the “Parenting strategies questionnaire” for adequacy,^[29]^ the “Utilization and Cost Questionnaire” for cost,^[30]^ and the “levels of institutionalization” scale for coverage.^[31]^ With regard to fidelity, no evidence-based instrument could be identified; thus, the fidelity will be assessed by comparing the protocol of the intervention with what will be done in the field, the education sessions will be videotaped and a second researcher will be invited to evaluate the fidelity.

To evaluate the impact of the intervention, many pre-tests will be performed before starting it: the COPD assessment test (CAT)^[32]^ to evaluate the quality of life of participants, the COPD clinical questionnaire (CCQ)^[33]^ to evaluate their respiratory health status, and the “Hospital Anxiety and Depression” (HAD) scale to measure the anxiety.^[34]^ Skills and expertise of the participants will be assessed using questions created for each session and comparing the pre- and post-intervention educational diagnosis. The hospital register of each participant will be consulted to collect and evaluate the number of hospitalizations and emergency room visits during the year preceding the intervention and during the intervention.

All these measurements will be grouped into evaluation sheets. There will be sheets to collect data from participants, and others to collect data from researchers so that the program can then be evaluated.

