#### First phase

2.6.1

In the first phase of our intervention the quality of life of participants, their respiratory health status, and their level of anxiety will be measured using specific tools. Participants’ skills and expertise will be evaluated by an educational diagnosis. The hospital register of each participant will be consulted to collect the number of hospitalizations and emergency room visits during the year preceding the intervention. Patients will be asked, at the end of the session, to complete sheet 1 of the evaluation that includes 4 parts about their perception of the acceptability, adequacy, adoption, and cost of the program.

A 2-part sheet about the cost and fidelity will be completed by 2 researchers. The cost part will be completed by the principal investigator after each nursing consultation. The fidelity part will be completed by a second researcher who will be invited to participate in the evaluation of the program. All sessions will be video or audio recorded to facilitate this task (Fig. 3).

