#### Phone call follow up

2.6.4

One month after the last intervention, using the phone, a third evaluation of the quality of life of participants, their respiratory health status, and their level of anxiety will be performed by the principal investigator who will also identify the rate of re-hospitalization and emergency visits for each participant in the month that follows the end of the intervention. The principal researcher will then complete the cost part of the 2-part sheet.

Researchers will complete the first part concerning the cost, which will be completed by the principal investigator. A second researcher will complete the fidelity part in addition to the Loln questionnaire that assesses coverage.

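### The prior-year baseline for hospital use comes from one hospital's register, and nothing ensures that the patient's admissions and emergency visits in that year took place there

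*Protocol article*

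**What the plan says.** Aim 2 (Abstract and Introduction) is to pre-test the impact on quality of life, emergency visits and rehospitalization. Section 2.1 describes a single-group study at one hospital: "It will be conducted at the Hôtel-Dieu de France (HDF) hospital, one of the largest university hospitals in Beirut".

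**Source of the counts.** Section 2.5 uses the hospital register for the "number of hospitalizations and emergency room visits during the year preceding the intervention and during the intervention". Section 2.6.1 repeats this for the baseline: "The hospital register of each participant will be consulted to collect the number of hospitalizations and emergency room visits during the year preceding the intervention". The Abstract names the same source. For the period after the program, section 2.6.4 has the principal investigator, at the telephone follow-up, "identify the rate of re-hospitalization and emergency visits for each participant in the month that follows the end of the intervention".

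**Who can enter.** Section 2.3 states that the "patient must be adult (18 years of age or older), male or female, outpatient, with moderate (Gold 2) or severe (Gold 3) COPD", and adds conditions on cognition, health status and consent. The exclusions concern other matters: "Patients will be excluded if they are diagnosed with lung cancer or if they have cognitive problems related to memory loss or speech disorders". Patients are "recruited based on the judgment of the pulmonologists at HDF hospital and on a voluntary basis from 30 patients". Under Phase I (section 2.4) the approach is open to anyone who has just been seen: "At the end of a medical consultation, the doctor will offer the patient the opportunity to benefit from a nursing consultation and remote monitoring". No condition refers to earlier care at this hospital.

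**The concern.** With no control group, the patient's own prior year is the only comparator for hospital use. A hospital's register records what happened in that hospital. A patient who was admitted elsewhere eight months ago and later came to this pulmonology clinic meets every criterion, but that admission need not appear in the baseline count. The same holds for a long-standing patient of the clinic who used another emergency department.

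Incomplete counts alone would not distort a before/after ratio. The risk comes from a difference in completeness between the two periods. Before entry the article names only the register. After entry the patient sees the nurse weekly, attends a final consultation and is reached by telephone one month later, when rehospitalizations and emergency visits are identified. If those contacts bring out events at other hospitals, part of the later period is counted more fully than the baseline. The baseline rate is then too low relative to the later rate, and a real reduction is understated or hidden. Expressing both periods as rates per unit time does not cure this, because it corrects window length and not completeness.

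**Working it through.** **No figure to reproduce.** The article gives no event rate, no share of care received elsewhere and no target effect for hospital use. Its only design figure is the sample of 30 (section 2.7), which lies within the cited range of 10 to 40 and has no bearing on this point. The check is therefore a comparison of sources, followed by illustrations.

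**Sources by window**

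| Window | Source named | Could events elsewhere be seen? |
|---|---|---|
| Year before (2.5, 2.6.1) | Hospital register | Not from the register |
| Intervention (2.5) | Hospital register | Not from the register; weekly contact might reveal them |
| Month after (2.6.4) | Identified by the principal investigator at the telephone follow-up | Possibly, if the patient is asked |

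**Formula.** Let R be the true rate ratio (after/before), u the share of prior-year events missed and v the share of later events missed. Then

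observed ratio = R × (1 − v) / (1 − u).

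If u = v, the observed ratio equals R and there is no bias. If u > v, the observed ratio is too high, that is, biased against the program.

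**Illustration A: no true effect (R = 1), nothing missed later (v = 0).** The ratio is 1/(1 − u).
- u = 10%: 1/0.90 = 1.11
- u = 20%: 1/0.80 = 1.25
- u = 30%: 1/0.70 = 1.43

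If the missed events belong to patients whose whole year was elsewhere, and those patients have the same event rate as the rest, these shares correspond to 3, 6 or 9 of 30 patients. At an assumed 0.5 events per patient-year, 30 × 0.5 = 15 true baseline events would be recorded as 13.5, 12 or 10.5.

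**Illustration B: assumed true R = 0.70, v = 0.**
- u = 20%: 0.70/0.80 = 0.875
- u = 30%: 0.70/0.70 = 1.00
- u = 50%: 0.70/0.50 = 1.40

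**Illustration C: only the telephone month is complete.** Take the intervention as 6 weeks (6/52.18 = 0.115 year) and the follow-up as one month (1/12 = 0.083 year), 0.198 year in all. If the register misses the same share u during the 6 weeks and nothing is missed in the last month, then v = u × 0.115/0.198 = 0.58u. With R = 1:
- u = 10%: (1 − 0.058)/0.90 = 1.05
- u = 20%: (1 − 0.116)/0.80 = 1.11
- u = 30%: (1 − 0.174)/0.70 = 1.18

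This case lies closest to the sources named in the article, and the bias is less than half that in A.

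**Against chance.** At 0.5 events per patient-year, 30 patients over 0.198 year give 30 × 0.5 × 0.198 = 2.97 events. The Poisson standard deviation is √2.97 = 1.72, or 1.72/2.97 = 58% of the mean. At 0.3 or 1.0 events per year the expected later counts are 1.8 or 5.9.

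**A zero is not evidence of a gap.** Under a Poisson model, exp(−0.3) = 74%, exp(−0.5) = 61% and exp(−1.0) = 37% of fully observed patients have no event in a year. A zero in the register is often genuine, so the register alone cannot show which patients were treated elsewhere.

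**The case against.** The strongest reply is that the difference in completeness is not documented. Nothing in the article sends patients to this hospital in an emergency; section 2.4 offers a telephone number only. Section 2.6.4 does not say that the patient is the source at the one-month call, and the principal investigator could consult the register again. If the register serves throughout and patients do not change hospital on entry, events elsewhere are missed alike before and after, and the ratio is unbiased. This stands. It makes the bias conditional, although the telephone contact makes better capture plausible for at least that month.

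Second, the article may not show every source. Figure 3 is not shown, the items of the Utilization and Cost Questionnaire are not visible, and a full protocol may say more. This also stands, but each time prior-year hospital use is described, the register is the only source named.

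Third, about 3 later events make chance far larger than a bias of 1.05 to 1.25, in a study whose main purpose is feasibility. That is correct, and it limits the weight of the point. It does not argue against a correction that costs almost nothing.

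A reader might infer three stronger things that the documents do not support:
- **That unobserved years are scored as zero.** No section says so, and coding rules of this kind are commonly left to the full protocol or analysis plan.
- **That newly diagnosed patients are unobserved.** A register of admissions and emergency visits does not depend on the date of diagnosis. The Introduction's figure of 80% undiagnosed comes from a national study and says nothing about patients at this clinic or where they were treated.
- **That later events are fully captured.** This is an assumption in illustrations A and B, not a statement in the article.

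**Conclusion.** The point holds in a limited form. The only comparator for hospital use is a 12-month count from one hospital's register, and neither the eligibility criteria nor the recruitment route ensures that the patient used that hospital in that year. Admissions and emergency visits elsewhere can therefore be missed at baseline. Capture may be better after entry, at least in the month covered by the telephone follow-up. If so, the baseline is understated and the comparison is biased against the program.

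The size cannot be derived. It depends on the difference between u and v, and the article gives neither. The ratios above show scale and are not estimates; with equal missing in both periods the bias is nil. The problem touches one impact outcome and leaves the feasibility outcomes alone. Section 2.7 presents the sample as adequate for sizing a later trial, but no section says that this event rate will be used for that purpose, so a knock-on effect is possible and not established. It is a cheap improvement, best made before enrolment starts.

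**What to change.** 1. At the Phase I nursing consultation, ask every patient about admissions and emergency visits at any hospital in the past 12 months, with hospital and approximate date.
2. Ask the same questions, in the same form, at the final consultation (for the intervention period) and at the one-month call (for the month since).
3. Read the register for all three windows. Match patient reports to register entries by date so that no event is counted twice.
4. Report register-only and combined counts for each window. Agreement in the before/after picture between the two series would be reassuring; a difference would show how much events elsewhere matter.
5. Treat a prior year covered by neither source as missing and not as zero, and state how many patients this concerns.

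Eligibility stays unchanged. Requiring earlier follow-up at this hospital would not close the gap, because established patients can also use other hospitals.

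The cost is a few questions at contacts already planned, plus the matching. The drawback is recall error, which is likely to be larger over 12 months than over the short later windows. Forgotten events would again lower the baseline, so the combined count is an improvement and not a complete cure, and the register-only series should stay beside it.

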### Data collection and follow-up

2.6

Figures 2 and 3 summarize all the phases and the different evaluations performed at each level.

**Figure 3 F3:**
[figure not shown]
Data collection and follow-up.

